## Abstract

**Background:**

Eye Movement Desensitization and Reprocessing (EMDR) is an evidence-based treatment for PTSD. However, it is unclear whether EMDR shows the same effectiveness in patients with substance use disorders (SUD) and comorbid PTSD. In this trial, we examine the effectiveness of EMDR in reducing PTSD symptoms in patients with SUD and PTSD.

**Methods/Design:**

We conduct a single-blinded RCT among 158 patients with SUD and comorbid PTSD admitted to a German addiction rehabilitation center specialized for the treatment of patients with SUD and comorbid PTSD. Patients are randomized to receive either EMDR, added to SUD rehabilitation and non-trauma-focused PTSD treatment (TAU), or TAU alone. The primary outcome is change from baseline in PTSD symptom severity as measured by the Clinician-Administered PTSD Scale at 6-month follow-up. Secondary outcomes are change from baseline in substance use, addiction-related problems, depressive symptoms, dissociative symptoms, emotion dysregulation and quality of life. Assessments are carried out by blinded raters at admission, at end of treatment, and at 3- and 6-month follow-up. We expect that EMDR plus TAU will be more effective in reducing PTSD symptoms than TAU alone. Mixed models will be conducted using an intention-to-treat and per-protocol approach.

**Discussion:**

This study aims to expand the knowledge about the effectiveness of EMDR in patients with SUD and comorbid PTSD. The expected finding of the superiority of EMDR in reducing PTSD symptoms compared to non-trauma-focused PTSD treatment may enhance the use of trauma-focused treatment approaches for patients with SUD and co-morbid PTSD.

**Trial registration:**

German Clinical Trials Register: DRKS00009007; U1111-1172-9213. Retrospectively registered 01 Juni 2016.

## Background

Up to 45% of the patients with SUD experience comorbid PTSD [1–3], indicating a clear need for PTSD treatment in this population. Although the importance of comorbid PTSD in the treatment of patients with SUD has been recognized [4], most SUD inpatient rehabilitation centers in Germany do not offer integrated treatment for SUD and PTSD. When an integrated treatment is offered, non-trauma-focused interventions are predominantly used to address PTSD [5]. This current clinical practice in routine SUD healthcare is in contrast to the national and international guidelines [6–8] that recommend trauma-focused treatment for PTSD, which clearly yields higher effect sizes compared with non-trauma-focused approaches. However, the evidence base of these guidelines is built on trials in which patients with PTSD and comorbid SUD have been almost continuously excluded [9, 10].

First evidence exists that trauma-focused treatments, such as prolonged exposure [11], trauma-focused imaginal exposure [12] and structured writing therapy [13], may also be effective in patients with PTSD and comorbid SUD in reducing PTSD symptoms, although the evidence is not consistent [13–15]. This trials also found that trauma-focused interventions for patients with SUD and comorbid PTSD could be applied securely without compromising substance use outcomes [14, 15]. This is an important result, because clinicians may hesitate to use trauma-focused therapy for patients with SUD and comorbid PTSD, because they might believe that eliciting intense emotions related to the traumatic event during trauma-focused treatment may increase the risk for relapse [16, 17]. EMDR is another trauma-focused treatment that has been shown to be effective in patients with PTSD alone [6, 18]. So far, no RCT has been conducted that examined whether EMDR is effective in reducing PTSD symptoms in patients with SUD and comorbid PTSD.

Trauma-focused PTSD treatment among patients with SUD may also effectively reduce SUD symptoms [19, 20]. Patients with PTSD and SUD report higher levels of craving in response to trauma-related cues [21] than patients with PTSD. Therefore, these patients might be more likely to use substances to regulate negative affective states associated with PTSD [20, 22, 23]. If negative affective states related to PTSD could be effectively reduced by trauma-focused treatment, SUD symptoms might also be reduced.

### Research aims and hypothesis

The primary aim of this study is to investigate the effectiveness of EMDR, added to SUD rehabilitation and non-trauma-focused PTSD treatment (TAU), in reducing PTSD symptom severity at 6-month follow-up compared with TAU alone in patients with SUD and comorbid PTSD. We hypothesize that EMDR combined with TAU will lead to a significantly greater reduction of PTSD symptoms than TAU alone, when comparing PTSD symptoms from baseline to 6-month follow-up. As secondary outcomes, we examine the effectiveness of EMDR on substance use-related outcomes, depressive symptoms, dissociative symptoms, emotion dysregulation and quality of life. If this study shows that EMDR can be used effectively in patients with SUD and comorbid PTSD, the results of this RCT might encourage a more frequent use of evidence-based trauma-focused treatments for patients with SUD and comorbid PTSD.

## Methods

### Design and study setting

This study is a rater-blinded 2-arms RCT. Assessments are scheduled pre-treatment (T0), post-treatment (T1), at 3-month (T2) and at 6-month (T3) follow-up. Participants are randomly assigned to either the EMDR plus TAU group or the TAU group. Data is assessed at an inpatient rehabilitation center in Germany (AHG Clinic Dormagen). This center is specialized for the treatment of patients with SUD (primarily alcohol use disorders) and comorbid PTSD. The study is coordinated by a research team of the Center for Interdisciplinary Addiction Research (CIAR), University Medical Center Hamburg-Eppendorf, Germany. The coordinating site is responsible for the study design, the training of the personnel involved in the data collection, the preparation and supply of all study documents, study monitoring, study supervision, data management and analysis, and reporting of the study results.

### Participants

We plan to recruit 158 adult patients with SUD and comorbid PTSD attending inpatient rehabilitation treatment from September 2015 to December 2017. Inclusion criteria are (1) age between 18 and 65 years; (2) DSM-5 diagnosis of a substance use disorder [24]; (3) DSM-5 diagnosis of PTSD or subsyndromal PTSD (criteria A and B and at least one of the criteria C to E) [18]; (4) capable to comprehend and speak German; (5) informed consent to participate in the study. Exclusion criteria are (1) severe dissociative symptoms according to the Dissociative Experience Scale [25] (total score > 40); (2) acute suicidality; (3) acute psychotic symptoms; and (4) severe cognitive impairments.

### Interventions

All patients included in this study participate in the usual treatment (TAU) of the SUD rehabilitation center provided for patients with SUD and comorbid PTSD. TAU includes SUD rehabilitation and non-trauma-focused PTSD treatment. TAU is present-focused and includes the provision of knowledge, techniques and skills to better cope with PTSD symptoms and to prevent SUD relapse (psychoeducation about PTSD and SUD; resource activation, e.g. establishing positive activities; imaginative exercises [26]; acceptance- and mindfulness-oriented skills [27]; elements of Seeking Safety [28], non-trauma-focused CBT). A treatment protocol was created prior to the start of the study that defines the intervention elements of the non-trauma-focused treatment. No processing of traumatic memories takes place in the TAU condition.

All study participants receive two 90-min and two 60-min non-trauma-focused group therapy sessions per week. In addition to the non-trauma-focused group therapy, participants randomized to the TAU group additionally receive one 50-min individual non-trauma-focused therapy session per week; participants randomized to the EMDR group receive one 50-min individual EMDR session per week. During an EMDR session, the patient focuses on a traumatic experience while simultaneously focusing on an external bilateral stimulus [29]. EMDR treatment follows standard EMDR protocols for processing memories of traumatic or stressful life events [30].

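### The comparison is stated as EMDR added to TAU versus TAU alone, but by the described schedule EMDR takes the place of the control arm's individual session

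*Protocol article*

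**What the plan says.** The add-on framing appears throughout the protocol article.

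- Abstract, Methods/Design: patients are randomized to "EMDR, added to SUD rehabilitation and non-trauma-focused PTSD treatment (TAU), or TAU alone".
- Research aims and hypothesis: the aim is to "investigate the effectiveness of EMDR, added to SUD rehabilitation and non-trauma-focused PTSD treatment (TAU), in reducing PTSD symptom severity at 6-month follow-up", and the hypothesis is that "EMDR combined with TAU will lead to a significantly greater reduction of PTSD symptoms than TAU alone".
- Design and study setting: "Participants are randomly assigned to either the EMDR plus TAU group or the TAU group".
- Statistical analysis, the opening of the Discussion, and the closing summary under Strengths and limitations all repeat the same contrast.

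The Interventions section begins in the same spirit: "All patients included in this study participate in the usual treatment (TAU) of the SUD rehabilitation center". It then sets out the weekly schedule. Everyone has two 90-min and two 60-min non-trauma-focused group sessions. For individual therapy, "participants randomized to the TAU group additionally receive one 50-min individual non-trauma-focused therapy session per week", whereas "participants randomized to the EMDR group receive one 50-min individual EMDR session per week". Nowhere is the EMDR arm said to have an individual non-trauma-focused session as well.

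One place is worded differently. The Discussion paragraph of the abstract gives the expected finding as EMDR being superior to non-trauma-focused PTSD treatment, which fits the schedule.

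**The concern.** An add-on trial and a substitution trial answer different questions. In an add-on trial, the experimental arm receives all that the control arm receives, plus the new element. The difference between arms then measures the gain from adding that element to existing care. In a substitution trial with equal contact time, the difference measures whether one form of therapy does better than another.

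The hypothesis fixes what the primary test on CAPS change at 6 months can be said to show. If the stated hypothesis is add-on and the delivered contrast is substitution, the primary result will be reported under the wrong description. This matters most for a null result. Under the schedule, it would mean that EMDR did no better than an active individual therapy of the same length. Under the stated hypothesis, it would be reported as no benefit from EMDR added to usual care.

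**Working it through.** **Inputs**, all from the Interventions section:

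- Group therapy, both arms: two 90-min and two 60-min sessions per week.
- Individual therapy, TAU arm: one 50-min non-trauma-focused session per week.
- Individual therapy, EMDR arm: one 50-min EMDR session per week.

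**Step 1: listed weekly time per arm.** Group time is 2×90 + 2×60 = 180 + 120 = 300 min in both arms.

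| | Group | Individual | Listed total |
|---|---|---|---|
| TAU arm | 300 | 50, non-trauma-focused | 350 |
| EMDR arm | 300 | 50, EMDR | 350 |

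The difference in listed time is 350 − 350 = 0 min/week. The arms differ only in the content of one session.

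**Step 2: what an add-on design would look like.** There are two possibilities.

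- TAU includes the individual session and both arms keep it: EMDR arm 300 + 50 + 50 = 400 min, TAU arm 350 min.
- TAU is the group programme only and the control arm has no individual session: EMDR arm 300 + 50 = 350 min, TAU arm 300 min.

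The Interventions section describes neither 400 versus 350 nor 350 versus 300.

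**Step 3: can either definition of TAU save the label?**

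- If the individual non-trauma-focused session is part of TAU, the EMDR arm lacks that part, and calling it EMDR plus TAU is inaccurate.
- If TAU is the group programme only, the control arm receives TAU and an extra individual session, so it is not TAU alone.

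The stated comparison fails under both.

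**Step 4: does the sample size depend on the label?** The Sample size calculation section gives 88 evaluable participants for a 15-point difference, SD 25, 80% power and α = 0.05. With a two-sided test, the normal approximation and 1:1 allocation:

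n per arm = 2 × (1.960 + 0.842)² × (25/15)² = 2 × 7.85 × 2.78 ≈ 43.6, rounded up to 44.

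The total is 2 × 44 = 88, and power at 44 per arm is 80.4%. The stated figure reproduces, and nothing in it changes with the wording of the arms.

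**The case against.** The strongest case for the plan is that this is loose labelling and misleads no careful reader. The Interventions section discloses both individual sessions, with their lengths, in one sentence. It defines TAU by content and not by a count of individual sessions. On that definition, the EMDR arm does receive TAU, through SUD rehabilitation and 300 min/week of non-trauma-focused group therapy. The article also condenses a fuller treatment protocol that is not shown.

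Part of this stands. The schedule is disclosed, and the content definition makes the EMDR plus TAU label defensible by itself. It does not rescue TAU alone as the name of the comparator, because that arm then has an individual session that the EMDR arm does not. Nor is this a detail left to a longer document: the article states both the schedule and the comparison, and they disagree. The Treatment fidelity section mentions adherence rating for individual SUD rehabilitation and non-trauma-focused treatment, but does not say that EMDR patients receive such sessions.

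A reader might draw several stronger inferences that the document does not support.

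- *The conclusion is misworded throughout.* The abstract's Discussion paragraph already words the expected finding as EMDR against non-trauma-focused treatment.
- *A positive result would be presented as support for extra sessions.* No section speaks of adding sessions. The aims and the closing summary speak only of more frequent use of trauma-focused treatment.
- *One seventh of therapy (50 of 350 min) is withheld from the EMDR arm.* The SUD rehabilitation programme is not itemised, so total therapy time is unknown and no such share can be computed.
- *The 15-point target is wrong for an active comparator.* The power analysis is taken from a trial of trauma-focused treatment plus usual substance use treatment against usual treatment alone. The 15 points are nevertheless presented as a clinically significant difference, and the document gives no figure suggesting another value.
- *The design is flawed.* Matching contact time is a reasonable design. Only its description is at issue.

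**Conclusion.** The point holds as an inconsistency between the stated comparison and the described treatment. On the schedule given, the trial estimates individual EMDR against individual non-trauma-focused therapy at 50 min/week each, on a shared background of SUD rehabilitation and 300 min/week of group therapy. The difference in listed therapy time is 0 min/week. The aim, hypothesis and arm labels claim the effect of adding EMDR to what the control arm receives, and no reading of TAU makes that true.

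This is more than a slip of wording, because it changes what the primary test can be said to show. It does not touch randomization, the outcome, the analysis model or the sample size. The conclusion rests on two assumptions: that the Interventions schedule is what is delivered, and that the SUD rehabilitation which is not itemised is the same in both arms. If EMDR patients in fact also have individual non-trauma-focused sessions, the schedule is the part that is misstated, and the sections still need to be reconciled.

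**What to change.** Reconcile the abstract (Methods/Design), Research aims and hypothesis, Design and study setting, Interventions, Statistical analysis, the opening of the Discussion, and the closing summary under Strengths and limitations. The investigators should state which weekly schedule each arm receives and whether the individual session is part of TAU.

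If the Interventions schedule is what is delivered, word the aim, hypothesis, arm labels and reported conclusion as: *individual EMDR versus individual non-trauma-focused therapy of equal length, both on top of SUD rehabilitation and non-trauma-focused group therapy*. The expected finding in the abstract's Discussion paragraph already fits this.

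The cost is wording only. No change to treatment, sample size or target difference is proposed.

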### Measures

#### Diagnoses of SUD and PTSD

To assess DSM-5 diagnoses of SUD and PTSD, all patients receive a semi-structured face-to-face interview at baseline (T0). The diagnosis of SUD is confirmed using the SUD section of the International Diagnostic Checklists for DSM-IV (IDCL) [31], adapted according to the changed SUD criteria in DSM-V. The IDCL is an established method for the assessment of psychiatric diagnoses. Studies have indicated good clinical practicability and satisfactory to excellent inter-rater and test-retest reliability [31, 32].

The diagnosis of PTSD is confirmed using the Clinician-Administered PTSD Scale (CAPS) [33, 34] for DSM-V [33, 34], which is an updated version of the CAPS for DSM-IV. The CAPS is considered the gold standard for PTSD assessment [35, 36]. The psychometric properties of the CAPS-IV have been reviewed [35] and indicate excellent convergent and discriminant validity, diagnostic utility, and sensitivity to clinical change.

#### Primary outcome

The primary outcome, change from baseline in PTSD symptom severity, is assessed using the CAPS for DSM-V [33, 34]. The interviewer evaluates the severity of each of the 20 DSM-V PTSD symptoms, based on a combined evaluation of the frequency and intensity on Likert-type scales (0 = asymptomatic, 1 = mild/subthreshold, 2 = moderate PTSD/above threshold, 3 = severe/markedly increased, 4 = extreme). The 20 DSM-5 PTSD symptom severity scores are then summed up to derive a total severity score, ranging from 0 to 80. A change of 15 points on the CAPS is considered clinically significant [35].

#### Seconday outcomes

Secondary outcomes include change from baseline in severity of substance use, addiction-related problems, dissociative symptoms, depressive symptoms, emotion dysregulation and quality of life (Table 1).

**Table 1 Tab1:** Measures and assessment points used in the study

Variable	Measure	Assessment method	T0 Baseline	T1 Post treatment	T2 3 months	T3 6 months
SUD diagnosis	IDCL [31]	interview	x	x	x	x
PTSD diagnosis	CAPS [33]	interview	x	x	x	x
PTSD symptoms	CAPS [33]	interview	x	x	x	x
Early traumatic experiences	CTQ [46]	self-report	x	x	x	x
Substance use	AUDIT [37]/DUDIT [40] TLFB [41]	interview	x	x	x	x
Addiction-related problems	ASI-Lite [42]	interview	x	x	x	x
Dissociative symptoms	DES [25]	self-report	x	x	x	x
Depressive symptoms	BDI-II [43]	self-report	x	x	x	x
Emotion dysregulation	DERS [44]	self-report	x	x	x	x
Quality of life	SF-12 [45]	self-report	x	x	x	x
Safety	SAE Report Form	self-report	----------------		x	x

*Notes. IDCL* International Diagnostic Checklists. *CAPS* Clinician-Administered PTSD Scale. *CTQ* Childhood Trauma Questionnaire. *AUDIT* Alcohol Use Disorders Identification Test. *DUDIT* Drug Use Disorders Identification Test. *TLFB* Timeline Follow Back. *ASI-Lite* Addiction Severity Index-Lite. *DES* Dissociative Experience Scale. *BDI-II* Beck Depression Inventory-II. *DERS* Difficulties in Emotion Regulation Scale. *SF-12* Short-Form 12-Item Health Survey. *SAE* Serious Adverse Event

Change from baseline in severity of substance use is measured by the Alcohol Use Disorder Identification Test (AUDIT) [37, 38] or the Drug Use Disorder Identification Test (DUDIT) [39, 40], respectively, depending on the type of the patients’ primary substance dependence. As additional substance-related outcomes, the mean amount of substance use per day and the number of non-consuming days within the last month is measured with the Timeline Follow Back (TLFB) [41]. Changes in addiction-related problems are assessed by the Addiction Severity Index-Lite (ASI-Lite) [42].

Change in dissociative symptoms (Dissociative Experiences Scale, DES) [25], depressive symptoms (Beck Depression Inventory-II, BDI-II) [43], emotion dysregulation (Difficulties in Emotion Regulation Scale, DERS) [44] and quality of life (Short-Form 12-Item Health Survey, SF-12) [45] are also assessed. The type and severity of early traumatic experiences are measured using the Childhood Trauma Questionnaire (CTQ) [46]. Sociodemographic data of the patients are measured by an interview using a sheet designed according to the documentation standards for the evaluation of addiction treatment [47].

Serious Adverse Events (SAEs; hospitalization, life-threatening event, disability or permanent damage, death) are measured by SAE Reporting Forms (date; initials of reporting person; participant study number and participant date of birth; SAE description; start date and duration of event; action required; action with regard to intervention; date of last intervention session; causality to intervention or assessment).

### Study procedure

At the patients’ admission to the rehabilitation center, a clinical psychologist informs the patient about the study and screens the patient according to the inclusion and exclusion study criteria. Patients that are potentially eligible for the study and consent to participate will receive the baseline assessment (T0) within the first days after admission (Fig. 1). If all inclusion and no exclusion criteria are fulfilled, the patient will be randomized to one of the two study arms. Additional data assessments are conducted at end of treatment (T1), as well as at 3-months and 6-months follow-up (T2 and T3, respectively). The interviews at T0 and T1 are conducted face-to-face, the interviews at T2 and T3 are conducted by telephone. To promote participant retention and complete follow-up, participants will be contacted several times between the assessments. The coordinating study team monitors the study procedure and traces back potential Serious Adverse Events during the study.

**Fig. 1 Fig1:**
[figure not shown]
Participant flow diagram

### Sample size calculation

Based on the results of the power analysis of a first RCT examining the effects of a trauma-focused PTSD treatment plus usual substance use treatment vs. usual substance use treatment ﻿alone﻿ in patients with PTSD and SUD [11], using the Clinician-Administered PTSD Scale (CAPS) as primary outcome, a sample size of 88 participants is required to achieve 80% power to detect a clinical significant difference of 15 points (SD = 25) in PTSD symptoms at 6-months follow-up, using mixed models with a .05 α-level of significance. In line with the dropout rates reported in previous intervention studies using rehabilitation inpatients [48, 49], a dropout rate of 40% is expected at 6-month follow-up. Consequently, we aim to include 158 participants in our study.

### Statistical analysis

Summary tables will be provided for all baseline, end of treatment and follow-up variables. Data will be summarized using frequency tables and descriptive statistics (mean, standard deviation, number and percentages of cases). Intention-to-treat and per-protocol analyses will be conducted for all outcomes. Missing data will be imputed using multiple imputation or a similar strategy.

To test the hypothesis that EMDR plus TAU will more greatly reduce PTSD symptoms than TAU alone, a linear mixed model will be calculated. Changes in PTSD symptom severity at 6-month follow-up as measured by the CAPS will be the primary outcome of the study and will be compared between the EMDR plus TAU and TAU group. The analysis will be adjusted for covariates that might be unbalanced between the groups (e.g., sex, type of trauma, treatment time spent in rehabilitation center), as well as for different baseline CAPS scores. The same procedure will be applied for secondary outcomes.

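### Treatment time in the rehabilitation center is named as an adjustment covariate for the primary and secondary models, although it accrues almost entirely after randomisation

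*Protocol article*

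**What the plan says.** The Statistical analysis section compares CAPS change at 6 months between EMDR plus TAU and TAU in a linear mixed model, with intention-to-treat and per-protocol analyses for all outcomes. On adjustment it states that the analysis will be "adjusted for covariates that might be unbalanced between the groups (e.g., sex, type of trauma, treatment time spent in rehabilitation center"), and baseline severity enters as well: "as well as for different baseline CAPS scores". The rule reaches beyond the primary outcome: "The same procedure will be applied for secondary outcomes".

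The order of events is in Study procedure. Consenting patients "will receive the baseline assessment (T0) within the first days after admission". After that, "If all inclusion and no exclusion criteria are fulfilled, the patient will be randomized to one of the two study arms".

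The Interventions section gives each arm one individual session per week, EMDR in one and non-trauma-focused therapy in the other. It states no fixed number of sessions or weeks.

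**The concern.** Randomisation balances, in expectation, what is fixed before allocation. Sex, type of trauma and baseline CAPS are of that kind. Treatment time is the realised length of a stay of which only the first days precede allocation. An arm difference in it could be chance, but it could also be a consequence of treatment, and the plan's wording treats it as an imbalance to be adjusted away.

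If EMDR changes how long patients stay, adjusting for stay does two things. It removes whatever part of the effect on CAPS runs through longer or shorter treatment. It also compares patients with equal stay who reached that stay for different reasons in the two arms, so any unmeasured cause of both stay and outcome confounds the comparison. The coefficient would then no longer be the intention-to-treat contrast that the trial sets out to estimate, for the primary outcome or for the secondary outcomes under the same rule.

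**Working it through.** **Timing.** The sequence is admission, T0 in the first days, randomisation once eligibility is confirmed, weekly individual sessions, end of treatment (T1). Treatment time is complete only at the end of treatment, so all but the first days of it follow randomisation. With one individual session per week, it also stands in for treatment dose.

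**Inputs from the document.** Difference 15 points, SD 25, alpha .05, power 80%, 88 evaluable patients, 158 randomised, 40% dropout (Sample size calculation). The plan's 88 reproduces: n per arm = 2 × (1.960 + 0.842)² × 25² / 15² = 43.6, so 44 per arm and 88 in total. For the check, 158 × 0.6 = 94.8, taken as 94 evaluable (47 per arm). The standard error of the contrast is 25 × √(2/47) = 5.2 points.

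**Inputs assumed.** The document gives no figure for any of these:
- shift in stay caused by EMDR: -0.3, 0, +0.3 or +0.5 SD of stay;
- causal effect of stay on CAPS change: 0 or -7.5 points per SD;
- unmeasured shared cause: absent, or with loading 0.5 on stay and -0.5 × 25 = -12.5 points on CAPS change.

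**Formula.** In a linear model, adjusted estimate = total effect - (shift × within-arm slope of CAPS change on stay). The slope is the causal effect of stay plus the part due to the shared cause:
- A, causal effect only: -7.5
- B, shared cause only: 0 + 0.5 × (-12.5) = -6.25
- C, both: -7.5 - 6.25 = -13.75

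For example, with shift +0.5 and case C: -15 - (0.5 × -13.75) = -8.1.

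**True total effect -15.** Each cell gives the formula value, then the mean and the power of the stay-adjusted test from 4,000 simulated trials:

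| Shift in stay | A | B | C |
|---|---|---|---|
| 0 | -15.0; -14.9; 0.86 | -15.0; -15.0; 0.84 | -15.0; -14.9; 0.92 |
| +0.3 SD | -12.8; -12.6; 0.69 | -13.1; -13.3; 0.74 | -10.9; -10.9; 0.69 |
| +0.5 SD | -11.3; -11.2; 0.59 | -11.9; -12.0; 0.63 | -8.1; -8.2; 0.44 |
| -0.3 SD | -17.3; -17.4; 0.93 | -16.9; -16.7; 0.90 | -19.1; -19.2; 0.99 |

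Without treatment time in the model, the estimate was -14.9 to -15.1 and power 0.81 to 0.83 in every row.

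**True total effect zero.** With a shift in stay, the adjusted estimate moved by 1.8 to 6.9 points in absolute value, and the test rejected no total effect in 6% to 33% of trials. Without treatment time it rejected in about 5%. With no shift, both models rejected in about 5%.

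Case B shows that stay need not affect CAPS at all for the estimate to move; a shared cause is enough.

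**Limits of the check.** It uses a single-time-point linear regression in place of the mixed model and ignores selective dropout. It shows the mechanism and the order of size, and is not a forecast.

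**The case against.** The strongest objection is that the harm is conditional. Nothing in the document says that EMDR alters length of stay or what determines it. With no shift, adjustment leaves the estimate at about -15 and even gains precision (power 0.84 to 0.92 against 0.81 to 0.83). This stands. A reader might infer that the planned estimate is certainly biased; the document does not support that. What remains is that the confirmatory contrast should not depend on an untested condition, and the plan itself lists stay among the variables that could differ between arms.

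The list is also open: treatment time is an example of a covariate that might be unbalanced, so it is a named candidate and not a certain term. That is correct. But nothing in the article limits adjustment to baseline variables or names a baseline-only model as primary. An unseen analysis plan may settle the final list, but naming this variable is an affirmative statement in the article.

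Two stronger readings do not hold:
- A reader might infer that choosing covariates by imbalance itself loses the randomised effect. For true baseline covariates it does not. In a simulation with five such covariates, each correlated 0.3 with outcome and selected at p < 0.10, the estimate was -14.9 for a true -15. Type I error was 0.032, and power was 0.845 against 0.966 with all five prespecified. The cost there is power and calibration. Selection by observed imbalance is in any case only the natural reading of the sentence, and the Blinding section keeps analysts blind to allocation.
- A reader might take the Background as voicing a worry about retention. It reports clinicians' possible belief about relapse and does not mention early discharge. That EMDR could change stay is an inference.

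**Conclusion.** The point holds in conditional form. The plan names a variable observed almost entirely after randomisation as an adjustment covariate for the primary model and, by the same rule, for the secondary outcomes. If allocation changes length of stay, the adjusted coefficient is not the intention-to-treat effect; if it does not, no harm follows.

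The document fixes neither size nor direction. Under the assumed shifts and slopes, a true -15 points is estimated between about -8 (EMDR lengthens stay) and -19 (EMDR shortens stay), a displacement of roughly 2 to 7 points against a standard error of 5.2. Blinding of analysts does not cure this, because the problem lies in what the model conditions on.

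**What to change.** In the Statistical analysis section, delete treatment time from the adjustment set of the primary and secondary intention-to-treat models. Restrict adjustment to variables fixed before randomisation: baseline CAPS, sex and type of trauma, all of which the section already names. Report treatment time descriptively by arm. If a stay-adjusted model is of interest, present it as a labelled secondary analysis that does not estimate the intention-to-treat effect.

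The cost is a one-sentence change before the analysis, with no new data and no change to conduct.
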